### Session overview

The study includes only pre−/post-flight sessions comprising different measurements, listed below and illustrated in Fig. 1:

Magnetic resonance imaging (**MRI**)Cervical spine **3D kinematics**an **Integrated Protocol** consisting of maximal and submaximal voluntary contractions of the neck muscles, an endurance test of the neck muscles, a neck muscle fatigue test and questionnaires;a dual energy X-ray absorptiometry (**DXA**) examination of the cervical spine

**Fig. 1 Fig1:**
[figure not shown]
Overview of Measurement Protocol

In addition to the longitudinal study of the astronauts, it would be desirable to compare the different measures in the astronauts to age and sex matched controls, which could be added as an expansion of the primary study set-up. In this case, the spacing of the tests will be aligned to be a similar duration as per the reference ISS subject. Two subjects on ground will be recruited per ISS subject. If possible, non-flier astronauts shall be recruited.

### Magnetic resonance imaging (MRI)

MRI Measurements will be done for:The intervertebral disc and vertebral body morphology and signal characteristics (sagittal T2 relaxography, DIXON and DWI imaging. Scan region: C2 to and including T1)Cervical musculature morphology and composition (paraxial: DIXON, T1-weighted imaging. Scan region: base of occiput to C7)

A Siemens Biograph 3 T scanner will be used for the measurements in Cologne, while measurements in Houston will be conducted with a Siemens Magnetom Verio 3 T.

#### Subject position

The subject shall be placed supine with a standard pillow and the head in neutral rotation. To fix the head in the neutral position, foam shall be placed between the head coil and the head of the subject.

### Cervical spine 3D kinematics

The helical axis approach shall be used to examine aberrations and impairments in cervical spine movement [28–30]. The helical axis model defines a movement as the angle of rotation around a moving axis and provides information about the instantaneous helical axis itself, the instantaneous centre of rotation and the range and speed of the movement. The helical axis shall be determined based on 3D motion capture of reflective markers defining a three-dimensional coordinate system for the head and the trunk [31]. For these measurements, the subject shall be equipped with retroflective markers attached to a headframe and to the trunk (Fig. 2). Depending on the size of the room and the position of the cameras in the room, the marker set may be supplemented by additional technical markers or marker arrays to reconstruct the required anatomical markers.

**Fig. 2 Fig2:**
[figure not shown]
Sample marker set to determine the three-dimensional coordinate system for head and trunk segments and to calculate the helical axis of rotation. Depending on the position of the cameras in the room, the marker set needs to be adjusted and may differ slightly from the image (The images are original pictures taken by the team)

The subject shall be instructed to perform the neck movements (neck flexion and extension, neck rotation, neck lateral flexion, circumduction) whilst seated, during which the kinematics of the movements are recorded using an infrared-based motion capture system. Three to five repetitions shall be performed for each of the movements in the same order as listed above. Between each movement, a rest period of at least 30 seconds should be provided. In all directions, the subject shall bend as far as possible, under the condition that the movement is painless, with a self-chosen pace. Helical axis descriptors are calculated using the equations described by Spoor and Veldpaus [32].

### Integrated protocol

The following table (Table 1) illustrates the Integrated Protocol in order of execution and respective measurement methods.

**Table 1 Tab1:** Integrated Protocol Overview

	Variable name	Measurement	2D High-density surface EMG	External force sensor	NIRS (blood flow and O_2_ consumption)	iPad/paper
1	**Clinical examination of muscle force, endurance, neuromuscular control**	Maximal voluntary contractions during: -Neck flexion and extension -shoulder shrug	X	X		
		Submaximal voluntary contractions during: -Neck flexion and extension -shoulder shrug	X	X		
		Endurance test: Sustained bilateral shoulder contraction	X	X		
2	**Neck muscle fatigue test:** **Neck extension**		X	X	X	
3	**Questionnaires**				X	X

### Examination of muscle force, neuromuscular control and endurance

The examination of neck muscle force, endurance and neuromuscular control will consist of maximal voluntary contractions (MVC), brief submaximal voluntary contractions tests, and an endurance test. During these procedures, high density, two-dimensional surface electromyography will be used to assess sternocleidomastoid, splenius capitis and upper trapezius (UT) activity over a large surface area during the contractions. The HDEMG electrodes will be placed only after the 3D Kinematics test is completed because the size of the electrodes would restrain the movement of the participant. Furthermore, a handheld dynamometer (NOD, OT Bioelettronica, Torino, Italy) will be used to measure the participant’s force applied during the different contractions. The OTBioLab+ software (OT Bioelettronica, Torino, Italy) will be used for HDEMG acquisition and to generate the force visual feedback targets for the submaximal contractions. During all tests, the participants will be seated on a stable chair, with their thorax strapped to the chair.

### Electromyography

The skin will be prepared prior to electrode placement. This will include shaving, gentle local skin abrasion with abrasive paste (Spes Medica, Italy) to reduce skin impendence and cleaning with water. HDEMG signals will be recorded using six 13 × 5 semi-disposable adhesive matrices of equally spaced electrodes (Fig. 3). The grids placed over the neck muscles will be smaller, with an inter-electrode distance of 4 mm (GR04MM1305, OT Bioelettronica, Torino, Italy), while those placed over the UT will have an interelectrode distance of 8 mm (GR08MM1305, OT Bioelettronica, Torino, Italy). The HDEMG grids will be prepared by attaching a double-side adhesive foam to the electrode (SPES Medica, Genoa, Italy) and the electrode cavities will be filled with a highly conductive-adhesive paste that provides electrode-skin contact (AC-CREAM, SPES Medica, Genoa, Italy). HDEMG signals will be recorded from each muscle bilaterally with the following electrode placement:Sternocleidomastoid: Approximately the first 1/3 of the distance between the line from the sternal notch to the mastoid process [33].Splenius capitis: From C7 to C2 at the intersection between the sternocleidomastoid and trapezius muscles along the muscle’s line of action (i.e. along a line connecting the top of the ear and C7) [34].Upper trapezius: 4th row of the electrode grid in line with C7 and the acromion [35–37].

**Fig. 3 Fig3:**
[figure not shown]
Electrode position over the participant’s **A**) sternocleidomastoid, **B**) splenius capitis and upper trapezius (The images are original pictures taken by the team)

Reference electrodes (WhiteSensor WS, Ambu A/S, Ballerup, Denmark) will be placed over C7 spinal process and right acromion. A wrist strap (WS1, OT Bioelettronica, Torino, Italy) will be also used as a reference electrode on the left side. All electrodes will be connected to the same bioelectrical amplifier (quattrocento- OT- Bioelettronica, Torino, Italy)

The HDEMG signals will be synchronized with the force signals acquired from the NOD handheld dynamometer (output range: 0-5 V, sampling rate: 100 Hz; Signal gain: 940 V/V) through the auxiliary input of the surface EMG amplifier. All HDEMG signals will be recorded in monopolar mode and a band-pass filter will be applied during the recording (bandwidth: 10–500 Hz, − 3 dB). Both HDEMG and force signals will be amplified by a factor of 150, sampled at 2048 Hz, and digitized with a 16-bit A/D converter through the bioelectrical amplifier.

#### Handheld dynamometer measurements

During the force measurements with the handheld dynamometer, the participants will be asked to perform maximal and submaximal voluntary contractions, with the aim to assess neck muscle strength and neck force control. The participants will perform neck flexion, extension and shoulder shrug. For neck flexion and extension tasks, the handheld dynamometer will be held against the participant’s forehead and occiput respectively (Fig. 4a and b). For the shoulder shrug, the handheld dynamometer will be placed over the participant’s acromion region and the investigator will resist the force exerted by the participant while they shrug their shoulder (Fig. 4c).

**Fig. 4 Fig4:**
[figure not shown]
Experimental setup for high-density EMG-force tests. **a** Neck flexion contractions, **b** neck extension contractions and **c** shoulder shrug contractions (The images are original pictures taken by the team)

##### Neck flexion and extension

During the maximum voluntary isometric contractions (MVC) and submaximal contractions of the neck flexors and extensors, the participant will be asked to cross his/her arms. They will be asked to flex and extend their neck against the resistance of the handheld dynamometer (isometric contraction) and two MVCs will be performed per direction. For the flexion and extension MVCs, the participants will be instructed to push maximally into the dynamometer. Submaximal contractions will be performed at 25 and 50% MVC and will last 20s and 15 s respectively and each contraction level will be performed twice for both flexion and extension. The order of the MVCs (extension/flexion) will be randomized across participants. For example, if the extension is to be tested first, the following procedures will take place: participants will perform one MVC lasting 5 seconds towards extension, rest for 1 minute, and then perform another MVC (5 seconds) in the same direction. The highest MVC will be used to determine the submaximal contraction forces, which will be presented to the participant in a computer monitor placed 60 cm in front of them. Participants will be instructed to match a force target represented as a trapezoid with a force ramp-up and ramp-down phase at a rate of 10%MVC/s, reaching the force target of 25 and 50% MVC. The submaximal contractions at 25 and 50% MVC will last 20s and 15 s respectively. The procedure is as follows: participants will perform two extension contractions at 25% MVC (20 seconds each), with 10s rest between repetitions and then after a 30s rest, another two extension contractions at 50% MVC with 20s rest between repetitions. The order of the submaximal contractions (force level: 25 vs. 50% MVC) will be randomized. The same procedures will be followed for isometric neck flexion contractions.

##### Shoulder shrug

During this measurement, the participant will be sitting on a chair with their arm and forearm extended with their palm facing their body. NOD hand-held dynamometer will be placed over the participant’s acromion region by the investigator who will resist the force exerted by the participant while they shrug their shoulder (Fig. 4c). Then, they will be instructed to shrug their shoulder against the investigator’s resistance. Only the dominant side will be assessed. Similar to the procedure for neck extension/flexion measurements, both MVC and submaximal contractions will be performed. The highest shoulder shrug MVC will be used to determine the shoulder shrug submaximal contraction forces, which will be presented to the participant on the same computer monitor.

#### Endurance test

Fatigability of the UT will be assessed via EMG during a single sustained bilateral shoulder contraction [36]. This test will be performed with the participant seated in the same position as during the previous measurements. The participants will be asked to abduct both arms without any resistance to 90 degrees with their elbows fully extended, their forearms in 90 degrees of pronation, and their palms facing towards the floor for 60s. One aluminium pole will be placed at shoulder level to provide tactile position feedback to the participant.

#### EMG signal processing & analysis

The EMG signal analysis will be performed offline, using a custom script (MATLAB 2020b, The MathWorks Inc., USA). As previously described, [35, 36], the HDEMG signals will be re-referenced offline to form 51 and 59 bipolar channels in the presumed direction of the muscle fibers, for the UT and neck flexors/extensors respectively. The bipolar EMG signals will be bandpass filtered (bandwidth: 20-350 Hz) and the Root Mean Square (RMS) values will be computed for each bipolar channel. Moreover, the average HDEMG amplitude, mean power spectral frequency (MNF) and modified entropy (a measure of the heterogeneity of muscle activity) will be calculated for each muscle [36, 38, 39]. These variables will be calculated for each task and repetition and for all six investigated muscles. The EMG amplitude will be expressed as a percentage of the maximum RMS value obtained during the maximal (baseline) MVC for each muscle. The level of co-activation between the neck flexors and extensors during the contractions will be also quantified as follows: EMGAntagonist/EMGAgonist * 100.

#### Single-motor unit identification

A previously validated algorithm will be also used to decompose the HDEMG signals into individual motor unit spike trains [40] The accuracy of the decomposition will be tested with the silhouette measure, which will be set to ≥0.9 [40]. The signals will be decomposed during the entire duration of the contractions, and the discharge times of the motor units will be transformed into binary spike trains from which all the motor unit firing descriptive statistics (i.e. discharge rate) will be calculated. The mean discharge rate and the discharge rate variability (coefficient of variation for the interspike interval [CoVisi]) will be determined during the stable plateau of force signal. Additionally, motor unit recruitment and de-recruitment thresholds will be defined as the neck flexion/extension/shoulder shrug force (%MVC) at the times when the motor units begin and stop discharging action potentials, respectively. Erroneous discharges will be visually inspected and edited using a custom algorithm [41]. Finally, motor unit activity will be monitored longitudinally [42] which allows tracking of the same motor units across different experimental sessions.

#### Force signal analysis

The force signals will be filtered prior to any calculations with a butterworth filter (bandwidth: 3-15 Hz). The highest peak force exerted during the MVCs (SI: kg) will be used as a measure of maximal neck flexion/extension and shoulder shrug strength for each participant. The absolute peak force values will be then normalised to participants’ body mass (N/kg). The neuromuscular control of all muscles will be assessed by calculating the amplitude of the force fluctuations of the force signal during the submaximal contractions in both absolute terms, as the standard deviation (SD) of the force signal and in relative terms as the coefficient of variation (CoV) of the force signal.

The EMG variables and the force related variables will be calculated for the same time window (i.e., steady part of all contractions), by using a custom-made MATLAB script.

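### A 3–15 Hz filter applied to force before every calculation removes the force level that peak MVC strength and the force CoV depend on

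*Protocol article*

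**What the plan says.** The rule stands in the protocol article under Force signal analysis: "The force signals will be filtered prior to any calculations with a butterworth filter (bandwidth: 3-15 Hz"). Four quantities follow in the same paragraph, and none is exempted:

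- Strength: "The highest peak force exerted during the MVCs (SI: kg) will be used as a measure of maximal neck flexion/extension and shoulder shrug strength".
- Strength relative to body mass: "The absolute peak force values will be then normalised to participants’ body mass (N/kg").
- Absolute steadiness: "in both absolute terms, as the standard deviation (SD) of the force signal".
- Relative steadiness: "in relative terms as the coefficient of variation (CoV) of the force signal".

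The preceding subsection, Single-motor unit identification, also uses a force level: "motor unit recruitment and de-recruitment thresholds will be defined as the neck flexion/extension/shoulder shrug force (%MVC") at the moments when a unit starts and stops firing.

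Two other places show what a two-number bandwidth means in this article. Under EMG signal processing & analysis: "The bipolar EMG signals will be bandpass filtered (bandwidth: 20-350 Hz"). In the recording description below Fig. 3, "a band-pass filter will be applied during the recording", with limits of 10 and 500 Hz.

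**The concern.** A band-pass filter passes what lies between its two edges and suppresses the rest. The contractions here are sustained: MVCs of 5 s, plateaus of 20 s at 25% MVC and 15 s at 50% MVC, and ramps of 10% MVC per second. The force level in such traces lies almost entirely below 3 Hz, so the filter leaves a signal that fluctuates around zero.

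Two entries in the Background's hypothesis list are at stake. The tenth (lower maximal neck strength) rests on peak force. The fourteenth (including reduced force steadiness) rests on the SD and CoV. If the rule is followed literally, a pre–post difference in the strength variable could come from faster or slower pushing, or from more or less tremor, with no change in strength. The CoV could not be interpreted at all.

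**Working it through.** There is no planning figure to reproduce. The check is whether each force variable survives the stated filter.

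**Inputs from the article.** Pass band 3–15 Hz; sampling at 2048 Hz; MVC of 5 s; ramp of 10% MVC/s, so 25/10 = 2.5 s to the 25% plateau and 50/10 = 5 s to the 50% plateau; plateaus of 20 s and 15 s.

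**Assumptions not in the article.** Filter order 2 or 4, run forward only or zero-phase; random force fluctuation of 2–3% of the level, with more power at low frequencies; true MVC of 100–300 N; rise times from 0.2 s up to 1.5–2 s.

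**Step 1: gain of the filter.** For a Butterworth band-pass of order n with edges 3 and 15 Hz (product 45, width 12), one pass has gain

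|H(f)| = 1 / √(1 + r^(2n)), with r = |f² − 45| / (12 f).

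| f | r | gain, n = 2 | gain, n = 4 |
|---|---|---|---|
| 0 Hz | infinite | 0 | 0 |
| 0.5 Hz | 44.75/6 = 7.46 | 0.018 | 0.0003 |
| 1 Hz | 44/12 = 3.67 | 0.074 | 0.006 |

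A zero-phase run squares these gains. The zero at 0 Hz holds for any order and either direction, and needs no assumption about force or noise.

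**Step 2: peak MVC force (simulation).** For a true 200 N the filtered peak is about 5–25 N, that is 5/200 = 2.5% to 25/200 = 12.5% of the true level. A 15 Hz low-pass returns about 207–215 N; the excess over 200 N is the simulated fluctuation.

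The filtered peak also depends on how fast the force rises. With the same true 100 N and 3% fluctuation:

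| Filter | rise 0.2 s | rise 2 s | ratio |
|---|---|---|---|
| order 2, zero-phase | 10.4 N | 3.1 N | 3.4 |
| order 2, forward | 13.1 N | 3.7 N | 3.5 |
| order 4, zero-phase | 8.9 N | 3.4 N | 2.6 |
| order 4, forward | 7.5 N | 3.2 N | 2.3 |

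Two contractions of equal strength thus differ about two- to threefold in the filtered peak. Force per body mass inherits this. The section also says that force variables are taken over the steady part of the contractions. If that covers the peak too, the onset drops out and only tremor remains.

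**Step 3: force CoV, 100 × SD/mean (simulation, 3% fluctuation).** After filtering, the plateau mean is at most 0.0013% MVC in absolute value, against a true 25 or 50. The CoV then ranges from about 40,000% to 800,000% in absolute value, with either sign. Unfiltered it is 2.7–3.2%; after a 15 Hz low-pass, 2.5–3.2%.

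**Step 4: absolute SD.** After filtering it is 0.38–0.43% MVC at the 25% plateau and 0.77–0.87% MVC at the 50% plateau, about half of the full-band SD. It stays finite and can be read as 3–15 Hz tremor.

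**Step 5: force in % MVC on the ramp (order 4, zero-phase).** True values of 5, 10, 20 and 40 read as 0.01, −0.13, 0.65 and 0.12 after the band-pass, and as 5.0, 9.7, 20.9 and 39.7 after a 15 Hz low-pass.

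**The case against.** The force sentence names a Butterworth filter and a bandwidth but does not say band-pass, whereas both EMG descriptions do. A condensed article may have merged a filter meant for the fluctuation measures with the strength paragraph; force tremor is a named hypothesis and 3–15 Hz suits it. This is a plausible account of how the sentence arose. It does not rescue the text: a filter with a 3 Hz lower edge is not a low-pass, and the sentence puts the filter ahead of every calculation.

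An analyst would also notice 200 N pushes reading as a few newtons, so a silently wrong strength result is unlikely. That stands for the practical risk. The filter would then be replaced by an unstated choice after the data were seen, in a study planned around 10 astronauts.

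A reader might infer more than the documents support:

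- *That every force variable is lost.* The absolute SD is not, and its band fits the tremor hypothesis.
- *That the submaximal contractions would be run at wrong levels.* The acquisition software generates the feedback targets from the MVC found in the session, so they are probably unaffected. The article does not, however, say that the strength outcome is taken from that in-session value.
- *That data are lost.* The force traces are recorded before this offline filter, so all variables can be recomputed.
- *That a hypothesis about recruitment thresholds fails.* None is listed, and the thresholds are defined in a different subsection that mentions no filter. For them this is a clarification.

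**Conclusion.** The stated rule is wrong for two outcomes: peak MVC force (with its body-mass version) and the force CoV. The certain part is structural: a 3–15 Hz band-pass has zero gain at 0 Hz, so neither a force level nor a mean force passes through it. This rests on reading the bandwidth as a band-pass, which the article's own usage supports.

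The sizes are illustrative. About 5–25 N for a true 200 N rests on the assumed fluctuation (2–3%), rise times (0.2–1.5 s) and filter orders (2–4). No single inflated CoV figure should be quoted, because the ratio has no stable value.

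The error is confined to the offline force analysis. The sample-size calculation rests on disc volume, and the MRI, DXA, kinematic, NIRS and EMG amplitude measures do not use this filter.

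**What to change.** In Force signal analysis, replace the blanket rule with two statements:

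1. Peak MVC force (and force per body mass) and the mean force in the CoV denominator are taken from an unfiltered or low-passed force signal, for example 15 Hz, with no lower cut-off. For clarity, say the same of the % MVC force used for recruitment and de-recruitment thresholds.
2. The 3–15 Hz band applies only to the SD of the force fluctuations, named as a tremor measure.

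Moving the SD itself to a low-pass is optional, since it is valid in its stated band. State which SD forms the CoV numerator, so that the ratio is fully defined.

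The cost is a sentence or two in the protocol and one line in the analysis script. No new data are needed, and the change is best made before any post-flight force data are analysed.

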### Neck muscle fatigue test

The Neck Muscle Fatigue Test consists of a sustained neck extension against a submaximal load measured with a handheld dynamometer at the occiput. For this test, the near-infrared spectroscopy (NIRS) will be performed using the PortaLite device (Artinis, Elst, Netherlands) to measure oxygen consumption in the neck skeletal muscles. HDEMG measurements will also be done during the fatigue test for the trapezius muscles only. All the 2D surface EMG grids from the previous tests shall be removed except of the grids placed on the trapezius muscle. The subject will be in sitting position and the NIRS sensors will be attached on the back of the subject’s neck with double-adhesive tape, one on each side on the paravertebral muscles above the level of C7 (Fig. 5a). Dark kinesiotape will be placed over the sensors to avoid artifacts from ambient light. The handheld dynamometer will be positioned at the occiput to monitor subject force output for targeting and feedback purposes. The measurements will be performed continuously before, during and after the neck muscle fatigue test. The NIRS sensors are connected via bluetooth to a laptop which will monitor the local muscle oxygen (StO_2_) in the tissue continuously.

